### Data Monitoring

Data monitoring will be performed by designated officials appointed by the ICMR headquarters in New Delhi.

### Ethical Considerations

The study was approved by the institutional ethics committee of Pondicherry Institute of Medical Sciences, Puducherry, India (IEC:RC/2023/83 on November 10, 2023) and the institutional ethics committee interventional studies of Jawaharlal Institute of Postgraduate Medical Education and Research, Puducherry, India (JIP/IEC/2024/03/30 on March 20, 2024). This study was registered with the Clinical Trials Registry–India (CTRI/2024/06/069220) on June 19, 2024. All participants will be recruited only after written informed consent is obtained from themselves or their legally authorized representatives. This study conforms to the requirements of the Declaration of Helsinki, 1964; the Indian Good Clinical Practice guidelines; and the ICMR-National Ethical Guidelines for Biomedical and Health Research Involving Human Participants, 2017. Personal information about the screened and enrolled participants will be collected, shared, and maintained to protect confidentiality before, during, and after the trial. Confidentiality of participation will be maintained, and personal identity will not be revealed during data collection, analysis, presentations, and publications. No compensation was provided for participation in the study. Study records will be made available only to authorized persons conducting the study and to the funding agencies without revealing participant identities. All data source documents, including clinical reports and records necessary for the evaluation and reconstruction of the clinical trial, will be stored securely for 5 years, with a focus on ensuring the study participants’ privacy and confidentiality.

## Results

A grant was received from ICMR-Safe and Rational Use of Medicines in December 2023 for this study. This study was scheduled to start from January 2024. The protocol preparation was completed with institutional ethics committee approvals and Clinical Trials Registry–India registrations. The scoping review examining international CMR practices and their adaptability to Indian health care settings was completed adhering to JBI (Joanna Briggs Institute) methodology and PRISMA-ScR (Preferred Reporting Items for Systematic reviews and Meta-Analyses extension for Scoping Reviews) guidelines. The review examined CMR practices in older patients through a comprehensive analysis of 7747 studies published between 2010 and 2024. A systematic search was conducted across PubMed, Cochrane Central Register of Controlled Trials, Clinicaltrials.gov, Global Index Medicus, Lens.org, and WHO-International Clinical Trials Registry Platform by using the following search terms: medication review, collaborative review, prescription drugs, and aged, and only English language studies were included. All retrieved records were imported into Rayyan software for screening. Two reviewers independently screened the titles and abstracts against predefined inclusion criteria: hospitalized patients aged ≥60 years, original research, or protocols evaluating CMR interventions. Full texts of potentially eligible studies were retrieved and assessed independently. Disagreements at any stage were resolved through discussion or a third reviewer adjudication. The review investigated 3 key aspects: CMR team composition, tools for identifying potentially inappropriate medications, and CMR implementation processes in Indian health care settings.

Standard operating procedures for the CMR intervention have been developed through expert panel consultation. The implementation phase will enroll 280 older patients (aged ≥65 years) with polypharmacy (≥5 medications) between January and June 2025. Economic evaluation using time-motion studies and cost analysis will be conducted from July to August 2025, concurrent with semistructured interviews of health care professionals exploring implementation facilitators and barriers. Thematic analysis of qualitative data, cost-effectiveness calculations, and manuscript preparation will be completed by 2025.

Based on the results of this study, modules will be prepared, and workshops will be organized for the prescribers on CMR interventions. The research findings will be presented at national/international conference for large-scale public dissemination. The results of this study will be published in indexed peer-reviewed scientific journals. The full protocol, participant-level dataset, and statistical code will be made publicly available after the completion of the study.

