**Conclusions:**

This study can provide insights into the implementation and effectiveness of CMR and help to understand the facilitators and barriers to implementing interdepartmental CMR and the cost incurred in its implementation. Interprofessional teams will collaboratively review and optimize medications for older patients with multimorbidity in India—a strategy expected to enhance care coordination, improve clinical outcomes, and reduce health care costs.

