##### Quantitative Component

The study design was quasi-experimental preinterventional and postinterventional with the following components: (1) costs incurred for the implementation of CMR in Indian health care settings and (2) MAI, reduction in the percentage of inappropriate medications, postdischarge adverse events, and medication-related admissions.

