#### Follow-Up Phase

At discharge, the clinical pharmacist will assess the discharge prescription for the MAI score and potentially inappropriate medications. The percentage of acceptance of the suggestions given (by the CMR team during the admission) by the clinicians will also be recorded from the patient records. After discharge, the patients will be telephonically followed up by a trained field investigator for 30 days to inquire about any hospital admissions, visits to the emergency department, drug-related complications, and episodes of dizziness and falls. The AT-HARM10 tool will be used to identify the medication-related hospital admissions after discharge after obtaining the necessary permission from the authors. The detailed description of the study evaluations/measurements/assessments at various time points after CMR intervention is shown in Table 1.

A comparison of MAI scores and the incidence of potentially inappropriate medications before and after CMR intervention at admission and at discharge will predict the efficacy of CMR.

**Table 1 table1:** Description of the study evaluations/measurements/assessments after collaborative medication review intervention.

Event time points			Hospital admission (day 1)		During hospitalization (every third day until discharge)		Hospital discharge		
							Day X^a^		Day 30^b^

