**Assessments**									
	CMR team time	✓		✓		✓			
	Cost analysis	✓		✓		✓			
	Drug-related problem	✓		✓		✓		✓	
	Hospital admissions							✓	

^a^X refers to the day of discharge of the patient from hospital since admission.

^b^Day 30 refers to 30th day after discharge.

^c^START: Screening Tool to Alert to Right Treatment.

^d^STOPP: Screening Tool for Older Persons’ Prescriptions.

^e^MAI: Medication Appropriateness Index.

^f^CMR: collaborative medication review.

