#### Secondary End Points

The secondary end points were as follows:

Costs involved in the implementation of CMR in Indian health care settings (tertiary health care settings perspective).Change in the number of potentially inappropriate medications from hospital admission to discharge due to CMR.Change in the MAI score from hospital admission to discharge due to CMR.Number of medication-related hospital admissions from the day of discharge to 30 days post discharge.

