### Phase 5: Calculating the Costs Incurred in the Implementation of CMR From a Health System Perspective (Opportunity Costs)

The multitude of health care providers and payment schemes affects the cost of any health service delivered and the estimation methods used, as costs can differ significantly between health centers due to variations in the service type and structure. Accurate cost analysis requires thorough understanding of a health care facility’s functions and financing mechanisms to ensure that all expenses are considered. In this study, a comprehensive case record form will systematically document both direct and indirect costs related to the CMR process. This includes detailed information on the facility characteristics, human resources, infrastructure, equipment, and operational costs, allowing for an extensive evaluation of the economic impact of the CMR process through quantitative and qualitative data collection [11,12].

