### Study Variables and Tools

The study variables, namely, patient demographics (name, age, contact information) and medical history, including current and past medical conditions, allergies, and adverse drug reactions, will be collected with the help of a predesigned case record form that includes tools such as the MAI tool, the STOPP/START tool, and the AT-HARM10 tool, which will be used for data analysis. The economic evaluation will be conducted from a health system perspective. Detailed information will be collected on the facility characteristics, human resources, infrastructure, equipment, and operational costs, allowing for an extensive evaluation of the economic impact of the CMR process from a health system perspective. The collected information in the case record forms will also be entered electronically into the Research Electronic Data Capture (REDCap) software (Vanderbilt), improving the data quality and enabling central access to data (since this is a multicentric study).

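### The article announces cost-effectiveness calculations, but a single-group design that costs only CMR delivery can support an implementation-cost analysis and no more; the costing perspective is also stated two ways

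*Protocol article*

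**What the plan says.** The closing timeline in the Results section lists the remaining work: "Thematic analysis of qualitative data, cost-effectiveness calculations, and manuscript preparation will be completed by 2025". This is the only place where a cost-effectiveness analysis of this study is mentioned.

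The rest of the article describes something narrower:

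- **Design** (Study Design, Quantitative Component): "The study design was quasi-experimental preinterventional and postinterventional with the following components", the components being implementation costs on the one hand and medication appropriateness and post-discharge events on the other.
- **Effect** (Follow-Up Phase): "A comparison of MAI scores and the incidence of potentially inappropriate medications before and after CMR intervention at admission and at discharge" is what efficacy will be judged on.
- **Costs** (Phase 5): the case record form "will systematically document both direct and indirect costs related to the CMR process".
- **Cost comparison** (costing paragraph at the end of Data Management and Statistical Analyses): public against private facilities, with a regression of total CMR cost on facility characteristics. No comparison of CMR with no CMR is planned.
- **Timing** (Table 1, Assessments): the row "Cost analysis" is ticked on day 1, during the stay and at discharge, but not at day 30. Hospital admissions are ticked at day 30 only.
- **Perspective**: Secondary End Points gives "tertiary health care settings perspective". Study Variables and Tools says "The economic evaluation will be conducted from a health system perspective". The Objective, Phase 5, the costing paragraph and the Discussion also say health system.

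**The concern.** A cost-effectiveness result is normally read as an incremental one: the extra cost of the intervention over its alternative, divided by the extra effect over that alternative. With no group managed without CMR, the article offers no estimate of what would have happened to prescriptions, admissions or care costs otherwise. A ratio built from these data would divide the cost of delivering CMR by a change that may partly have occurred anyway, since prescriptions can change during a hospital stay for many reasons.

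How the result is read matters here. The Introduction cites benefit-to-cost ratios for medication review, including one from a cluster randomised trial. The Discussion says that the economic data will be directly relevant to policy makers and administrators. A crude ratio labelled as cost-effectiveness could be set beside those figures as if it were of the same kind. The Discussion's limitations cover purposive sampling, the tertiary setting and short follow-up, but not the lack of a control.

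The two perspectives are a separate matter. They decide which costs belong in the analysis, and a reader cannot tell which statement governs.

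**Working it through.** **Step 1. Does the sample size imply a comparator?** The article's only computed design figure is 280 (Sample Size Estimation and Analysis): 28% prevalence, effect 10%, power 80%, significance 5%. I read the effect as 10 points, 28% to 18%, and the test as two-sided; the article states neither.

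- Two-proportion formula, pooled proportion 0.23: n = [1.96 × √(2 × 0.23 × 0.77) + 0.842 × √(0.28 × 0.72 + 0.18 × 0.82)]² / 0.10² = 277 per time point.
- Paired (McNemar) formula with independent before and after status, discordance 0.28 × 0.82 + 0.72 × 0.18 = 0.359: n = [1.96 × √0.359 + 0.842 × √(0.359 − 0.01)]² / 0.10² = 280.
- Two independent groups would need 2 × 277 = 554 in total; 140 per group gives about 51% power.

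So 280 fits one cohort measured twice. This does not prove how the figure was obtained, but it agrees with the design text: no control group is built in. The figure is for efficacy, not for the economic analysis.

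**Step 2. What an incremental ratio needs, and what is available.** Write the ratio as [K + (R1 − R0)] / (E0 − E1), where K is the cost of delivering CMR, R is the cost of other care with (1) and without (0) CMR, and E is the number of potentially inappropriate medications at discharge.

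| Term | Available from the plan as described? |
|---|---|
| K | Yes: CMR team time, staff, infrastructure, equipment and operating costs |
| R1 | Not among the cost items described; post-discharge events are recorded, but no cost is ticked at day 30 |
| R0 | No: no group without CMR |
| E1 | Yes: discharge assessment |
| E0 | No: only the admission value A stands in for it |

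Putting A in place of E0 is right only if nothing would have changed between admission and discharge without CMR. For 30-day admissions there is not even a within-patient baseline.

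**Step 3. Size, under an assumption.** Let D = A − E1 be the observed fall and u the share of D that would have occurred without CMR. The crude ratio is K/D. The delivery cost per medication avoided by CMR is K/[D(1 − u)]. The second is 1/(1 − u) times the first:

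- u = 0.25: 1/0.75 = 1.33
- u = 0.50: 1/0.50 = 2
- u = 0.75: 1/0.25 = 4

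The article gives nothing from which to estimate u. If prescribing would have worsened without CMR, u is negative and the crude ratio errs the other way: at u = −0.25 the multiplier is 1/1.25 = 0.8. The term R1 − R0 cannot be sized at all.

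**Step 4. Perspective.** Secondary End Points names tertiary settings; the Objective, Phase 5, Study Variables and Tools, the costing paragraph and the Discussion say health system. An admission to another hospital after discharge is a health-system cost but need not be a cost to the study hospitals, so the two statements can lead to different cost lists.

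**The case against.** The strongest reply is that this is one phrase in a timeline. Everywhere else the economic aim is the cost of implementing CMR: in the Objective, the secondary end point, the Phase 5 title and the costing paragraph. The sentence just before the phrase speaks of time-motion studies and cost analysis. No ratio or effect denominator is defined, and the details may sit in the full protocol. This stands as far as it goes: the absence of method detail is no fault of an article. But no fuller text can supply a comparator that the described design lacks, and the phrase names a planned output.

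Several stronger readings are tempting, and the article does not support them:

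- **That Table 1 wrongly omits readmission costs.** The stated cost end point is implementation cost. Table 1 ends all CMR activities at discharge, so ending the costing there is coherent. It would be a gap only if a full economic evaluation were intended.
- **That no incremental cost of any kind can be estimated.** CMR adds pharmacist review, team meetings and written suggestions, and that added delivery cost can be measured directly. What cannot be estimated is net cost after offsets.
- **That the conflict of perspective makes the ratio non-incremental.** It does not; the missing comparator does. The tertiary wording may even be meant to name the setting, since the Discussion confirms the tertiary focus. It is still worded as a perspective.
- **That a cost-effectiveness figure is promised to ministries.** The Discussion says that policy briefs will summarise key recommendations, without naming such a figure. The abstract's Conclusions call CMR "a strategy expected to enhance care coordination, improve clinical outcomes, and reduce health care costs", which is an expectation and not a planned estimate.

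**Conclusion.** The point holds in a limited form. The design as described can estimate the cost of implementing CMR. It cannot estimate incremental cost-effectiveness or net savings, so announcing cost-effectiveness calculations claims more than the data can give. The perspective is also stated inconsistently and needs reconciling.

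This rests on the article's own account: one group, admission against discharge, costs of the CMR process only, and no cost contrast between CMR and no CMR. It does not rest on anything left to a fuller document. The multipliers of 1.33, 2 and 4 show how far a crude ratio could mislead under assumed values of u; they are not estimates for this study, and the direction is not guaranteed. The economic analysis is secondary and the primary end point is untouched, so the correction is modest but worth making before any result is reported.

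**What to change.** 1. In Results, replace the cost-effectiveness wording with a descriptive implementation-cost analysis: mean CMR cost per patient reviewed, with a confidence interval.
2. If a cost per potentially inappropriate medication resolved is reported, label it an average ratio based on an uncontrolled change, not an incremental ratio.
3. State one perspective in the Objective, Secondary End Points, Phase 5, Study Variables and Tools, the costing paragraph and the Discussion.
4. Draw no conclusion about cost-effectiveness or cost reduction from this study.
5. Only if the sponsor wants more than implementation cost under a health system perspective: value the day-30 drug-related admissions and emergency visits, and report the result as a descriptive total, not an effect of CMR. State which events count, because the exclusion criteria rule out readmissions and emergency visits that are not drug-related. The article lists events but no length of stay or resource use, so this step would need unit costs per event or some added data items.

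Items 1 to 4 are wording and labelling and need no new data. The downside is a more modest economic claim.

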## Discussion

This study will assess the feasibility of implementing CMR in Indian hospitals and identify the key facilitators and barriers to CMR implementation. This study will evaluate the potential for reducing potentially inappropriate medications and medication-related admissions while providing crucial cost-implementation data for the Indian health care context.

Although CMR implementations have been well-studied in Western health care settings, with documented reductions in potentially inappropriate medications and readmissions, this will be among the first studies to systematically evaluate CMR feasibility and implementation costs in Indian health care settings [3,8,13-17]. The protocol’s mixed methods approach will help bridge the knowledge gap between established Western practices and the unique challenges of the Indian health care system. By adopting a health system perspective for economic evaluation, this study will generate data of direct relevance to policy makers and administrators. However, purposive sampling in the qualitative component may introduce selection bias, and the exclusive focus on tertiary care settings may limit the generalizability of the findings to primary or rural health care facilities. Additionally, the relatively short follow‑up period proposed in this protocol will constrain our ability to assess the long‑term sustainability and downstream clinical effects of CMR.

Upon completion of this study, subsequent research will aim to develop and pilot standardized training modules for clinical pharmacists, ensuring consistency in CMR workflows across institutions. Finally, the findings will inform the creation of national guidelines and policies to support the systematic integration of CMR into regular clinical practice throughout India. Policy briefs summarizing key recommendations will be developed for the Ministry of Health and Family Welfare and relevant state health departments.

The findings of this study will redefine medication management practices and pave the way for evidence-based, scalable models of CMR in resource-constrained settings. It will underscore the need for cross-disciplinary collaboration as a fundamental strategy to address multimorbidity in older adult populations, thereby offering valuable insights for policy makers and health care providers aiming to optimize geriatric care.

## Appendix

Multimedia Appendix 1 Interview guide for focus group discussions among the collaborative medication review team and clinicians.

Multimedia Appendix 2 Peer review report by the National Task Force on Safe and Rational Use of Medicine, Indian Council of Medical Research.

## Abbreviations

AT-HARM10: Assessment Tool for identifying Hospital Admissions Related to Medications-10 items
CMR: collaborative medication review
FGD: focus group discussion
ICMR: Indian Council of Medical Research
MAI: Medication Appropriateness Index
PRISMA-ScR: Preferred Reporting Items for Systematic reviews and Meta-Analyses extension for Scoping Reviews
REDCap: Research Data Capture
START: Screening Tool to Alert to Right Treatment
STOPP: Screening Tool for Older Persons’ Prescriptions
WHO: World Health Organization
